## Abstract

**Background:**

Families applying for asylum have often experienced multiple potentially traumatic events and continue to face stressors during their resettlement. Studies have indicated that traumatic events can negatively impact parenting behaviour and child development. A secondary preventive multi-family intervention programme, called Family Empowerment, was developed. Family Empowerment aims to strengthen parenting skills and prevent exacerbation of emotional problems in asylum-seeker families. This study protocol aims to evaluate the feasibility, acceptability, and potential effectiveness of Family Empowerment to reduce parental mental health problems and improve family functioning.

**Methods:**

An uncontrolled pre-test-post-test design will be conducted, using a mixed-methods approach. Approximately 60 families living at asylum centres and family locations with children aged 0–18 will be included. All participants will be invited to take part in seven sessions of Family Empowerment. Measurements take place at baseline, during implementation of Family Empowerment and 1 week post-Family Empowerment. Demographic data, the quality of the parent-child interaction, family functioning, parental symptoms of depression and anxiety, and participants’ feedback on progress and the therapeutic alliance will be assessed. A programme integrity list will be filled out during each session. Semi-structured interviews at baseline and post-Family Empowerment will be used to evaluate Family Empowerment.

**Discussion:**

This is the first study to provide a pilot implementation and evaluation of Family Empowerment. The current study will inform us on how to improve programme elements and the implementation of Family Empowerment. Limitations are discussed.

**Trial registration:**

Dutch Trial Register, TC = NTR6934. Registered on January 8 2018.

## Background

In 2017, approximately half of all refugees worldwide were minors below 18 years of age. Most of these minors arrived in the country of resettlement with at least one parent or caregiver. These refugee families have been forced to flee their homes as a result of persecution, violence, or conflict [1]. Many of them have been exposed to multiple potentially traumatic events prior to and during their flight, such as the loss of loved ones, war-related events, and physical violence. Furthermore, studies indicate that the continuous stressors refugees are exposed to during resettlement, including social and economic insecurities and long and complex asylum procedures, affect their psychological functioning [2, 3]. Table 1 describes the placement procedure of refugees applying for asylum in the Netherlands.

**Table 1 Tab1:** Placement of refugee families in the Netherlands

Refugees applying for asylum in the Netherlands first report to an ‘application centre’ where they receive shelter, medical care, and guidance. During the first phase of the asylum procedure, they are accommodated in a ‘process reception centre’. Asylum-seeker families are then placed in an asylum centre that provides them with basic needs, such as food and a roof over their heads, until their asylum application is granted or rejected. Children under the age of 18 have the right to shelter when their asylum application has been rejected. If the application is rejected and the family does not leave the Netherlands within 28 days, families are placed in a ‘family facility’, where they are prepared for deportation. In these centres, families have access to a limited level of facilities [4]. When the children turn 18, their right to shelter ends. As a result of the circumstances in family facilities, including limited financial resources, freedom-restricting measures, and insecurity concerning deportation, an increased level of distress can be expected here [5, 6].	

The accumulation of disruptive events and circumstances before and during the flight and the stressors inextricably linked with migration and resettlement can affect the psychological functioning of asylum-seeker families [2, 7]. Although studies indicate that most refugees do not develop mental health disorders, a substantial minority develops adverse emotional reactions and stress-related complaints, such as difficulty concentrating, sleeping problems, and irritability [8, 9]. Such complaints can impact the daily lives of refugee children, including their educational achievements, social functioning, and family interactions [9, 10].

Asylum-seeker children cannot be seen in isolation from the context and environment in which they grow up. Their parents often have to deal with their own distressing experiences, losses, and continuous stressors. As a result, they are at risk of developing stress-related complaints, which can undermine their parenting skills. For example, they can be less emotionally available, less structuring, and less supporting towards their children [11]. Additionally, exposure to traumatic situations can disrupt the parents’ and child’s capacity to mentalize, which refers to the ability to reflect upon and understand the state of mind of yourself and the other [12, 13]. A reduced capacity to mentalize may negatively affect the development of healthy attachment relationships between parents and their children and consequently affect the overall development of the child [12, 13]. However, clinical experience suggests that the detrimental impact of stress-related complaints on parenting skills can be counteracted by focusing on social and psychological support to help families adapt after distressing events [6, 9]. A recent review showed that studies focusing on preventive programmes addressing asylum-seeker families have been scarce so far [9].

Multi-family therapy (MFT) has been developed by Laqueur et al. [14] in order to improve family functioning and strengthen social support. MFT has since been adapted to meet the needs of various groups, including patients who suffer from symptoms of anorexia, schizophrenia, depression, and conduct disorder [15, 16]. MFT is a psychosocial intervention for a group of at least two families including at least two family members from different generations [17]. Since its development, MFT has been conducted with a variety of theoretical models, illnesses, disorders, and populations [18]. The frequency, duration, and number of sessions differ across settings and populations. Activities are adapted for each specific setting and population. MFT focuses on issues or concerns that families have in common and that are directly or indirectly related to family interactions. Sessions focus on strengthening interfamilial relations. For over 10 years, MFT has been provided to refugee families at the Foundation Centrum ‘45, a Dutch centre for specialist diagnostics and treatment of people with complex psychotrauma complaints.

At the Foundation Centrum ’45, MFT has, so far, mainly been offered to families with severe mental health problems and impaired family functioning. The main principles underlying MFT can also be applied in a preventive programme. Accordingly, therapists and researchers at the Foundation Centrum ‘45 developed a secondary preventive programme for asylum-seeker families based on MFT: Family Empowerment (FAME). FAME addresses families who live under stressful circumstances in asylum centres and family facilities and who may experience the impact of stress-related complaints on parenting, individual mental health, and family functioning. The programme addresses families with diverse cultural backgrounds. As described in more detail below, during FAME, a varying number of five to eight families gather in one room in weekly sessions of approximately 2–3 h for seven consecutive weeks. The aim is to reinforce parenting skills and social support, to improve family functioning and to prevent further development of emotional problems. FAME focuses on activating the families’ own resources and knowledge and allows families to exchange their perspectives, feedback, support, and knowledge. Skills can be developed and practised in a safe environment. Mentalization plays an important role in FAME, as the programme aims to stimulate reflection on one’s own and others’ thought processes and emotions [6].

Although FAME has previously been offered at a family facility, the effects of the programme have not yet been evaluated systematically [6]. Weine [19] proposed a cycle for developing and evaluating preventive programmes for refugee families based on empirical evidence. This cycle encompasses five steps, namely step 0, foundational activities; step 1, template preparation; step 2, situation-specific adaptation; step 3, intervention trial; and step 4, new situations. The development of the FAME manual is in line with both the foundational activities (step 0) and the template preparation (step 1) [6]. The manual describes programme elements that have been developed based on empirical evidence and clinical experience with refugees and MFT [6]. Step 2, situation-specific adaption, was conducted as the programme elements were adapted to fit the needs of asylum-seeker families living in asylum centres and family facilities. The resulting FAME programme adheres to the principles and approaches as described in the manual and incorporates situation-specific adaptations. The aim of the current study is to realize step 3 of the cycle proposed by Weine [19]: performing a pilot intervention trial, to demonstrate programme characteristics such as feasibility (whether the preventive programme is doable), acceptability (whether families and trainers accept the programme), and potential effectiveness (whether the programme coincides with positive changes in key outcomes). This precedes the final step (step 4), namely ‘new situations’, which includes conducting intervention trials at other sites and in other contexts.

### Objectives

The current pilot study aims to evaluate the feasibility, acceptability, and potential effectiveness of FAME to reduce parental mental health problems and improve family functioning. As families living in family locations might suffer from increased levels of distress, we expect these families to have more difficulties concerning the parent-child relationship, parental symptoms, and family functioning than families living in asylum centres. Therefore, baseline distress levels of both categories of families will be compared. Specifically, the objectives are to determine:Whether it is feasible to offer FAME to families living in Dutch asylum centres and family facilities.Whether FAME is acceptable to asylum-seeker families.Whether undergoing FAME coincides with a reduction in parental symptoms of anxiety and depression and improvement in family functioning.Baseline differences and similarities in the parent-child relationship, parental symptoms of anxiety and depression, and family functioning between families living in asylum centres and families living in family facilities.

## Methods/design

### Trial design

An uncontrolled, two-group pre-test-post-test design will be conducted, using a mixed-methods approach. Standardized questionnaires, semi-structured interviews, an observational scale, and a (self-constructed) programme integrity list will be used. The programme, including measurements, will take approximately 10 weeks per group.

### Participants

Study participants will be recruited from the asylum-seeker family population in the Netherlands. Families will be selected through convenience sampling. Eligible families must meet the following criteria: (1) at least one caregiver participates in FAME, (2) at least one child aged 0–18 participates, and (3) the family lives in an asylum centre or family facility. Participants who are not able to function in a group, as reported by health teams of the family facility or asylum centre, are not eligible for this study. For example, participants who are likely to experience difficulties communicating in a group setting as a result of severe psychiatric illness, such as psychosis, will be excluded. Families with psychiatric problems, such as posttraumatic stress disorder or depression, who are likely to be able to benefit from FAME are included in the study. This will be discussed with the health teams prior to inviting the families to take part in the information session about FAME. Each group will include approximately five to eight families. Families will be divided over the groups based on the age of their child (0–5, 6–12, 13–18). However, this division cannot be followed strictly, for example, because some families have children in more than one age category. Therefore, the division will be used merely as a guideline. If there are multiple children in a family, parents are asked with which child they experience most difficulties and will be allocated to the age group of that child. All children of the family are invited to take part in the programme.

As this is a pilot implementation and evaluation of a programme that has not been studied previously, it was not considered appropriate to conduct a reliable sample size calculation. We aim to include approximately five living locations. In each location, we will recruit two groups of approximately six families. This will result in a total sample size of approximately 60 families (5 × 2 × 6). One or two parents and approximately one to two children of each family will take part, resulting in a total number of approximately 90 parents and 90 children.

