### Statistical analysis

#### Analysis of quantitative data

Quantitative data-analysis will be conducted using SPSS 23 (IBM Statistics). Descriptive statistics of demographic data, the programme integrity list, and the rating scales will be presented for all participants. For continuous variables, means, standard deviations, medians, and ranges will be reported. For categorical variables, numbers and percentages will be reported.

To test the hypothesis that families living at family facilities have more problems concerning the parent-child relationship and family functioning and higher parental symptoms of anxiety and depression than families living at asylum centres, pre-test scores on the EAS, PHQ-4, and SCORE-15 will be compared between these two groups using independent *t* tests.

To evaluate whether undergoing FAME coincides with a reduction in parental symptoms of anxiety and depression and improvement in family functioning, differences between the pre- and post-test scores on the SCORE-15 and PHQ-4 will be calculated. If more than 40 participants have completed the pre- and post-test measures, a mixed-design ANOVA will be executed. However, if there is a large amount of missing data, or if less than 40 participants have completed pre-test and post-test measures, two independent *t* tests will be executed. In addition to statistical significance, it is important to report any meaningful clinical change when studying the impact of an intervention. Calculating the Reliable Change Index (RCI), as proposed by Jacobson and Truax [31], allows us to do so. Using the RCI, we will calculate whether the differences in the scores between *t*_1_ and *t*_3_ are greater than the measurement error. A calculated RCI larger than |1.96| indicates a clinically reliable change with 95% certainty. The RCIs allows us to determine the numbers of participants improved, unchanged, and worsened from *t*_1_ to *t*_3_.

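### The baseline comparison of family facilities with asylum centres is unadjusted, and child age may differ between the two by chance or local recruitment; an age-adjusted estimate, chiefly for the EAS, should stand beside it

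*Protocol article*

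**What the plan says.** All references are to the protocol article.

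- **Locations and groups (Participants).** "We aim to include approximately five living locations" and "In each location, we will recruit two groups of approximately six families". The split of locations between asylum centres and family facilities is not given. Families are a convenience sample.
- **Age bands (Participants).** "Families will be divided over the groups based on the age of their child", the bands being 0–5, 6–12 and 13–18 years. The section at once qualifies this: "However, this division cannot be followed strictly, for example, because some families have children in more than one age category". It adds: "Therefore, the division will be used merely as a guideline". A family with a child of any age from 0 to 18 is eligible at every location, and all its children are invited.
- **Analysis (Analysis of quantitative data).** "pre-test scores on the EAS, PHQ-4, and SCORE-15 will be compared between these two groups using independent" *t* tests. The hypothesis is directional, with family-facility families expected to do worse. No covariate is named.
- **Purpose (Objectives).** Objective 4 is worded as a description of baseline differences and similarities. The reason given for expecting a difference is greater distress in family locations, which Table 1 traces to circumstances in those facilities.
- **Data (Measurements).** The ages of family members and educational level are collected. The EAS scores every dyad on the same six components, whatever the child's age.
- **Limitations (Discussion).** Small sample size and convenience sampling are acknowledged in general terms. Child age is not mentioned.

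**The concern.** The two location types are not randomised, and each is represented by very few sites. Child age enters the formation of groups, there are two groups per location against three age bands, and no step described keeps the age mix similar between types. A 20-minute interaction with an infant and one with a teenager are scored on the same EAS scales, so a difference in child age could appear as a difference in emotional availability, or could hide one.

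This matters because the comparison is introduced with a reason rooted in living conditions, and readers will tend to interpret it that way. An unadjusted *t* test cannot show how much of a difference goes with child age. If the score does depend on age, adjustment would also remove some residual variance.

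The concern is weaker for PHQ-4 and SCORE-15. Both are parent self-reports, and the protocol gives no reason to expect them to vary with the child's age.

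**Working it through.** **The plan's own figure.** "This will result in a total sample size of approximately 60 families (5 × 2 × 6"). 5 × 2 × 6 = 60 families, which reproduces, or 12 per location.

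**Inputs from the protocol.** About 5 locations; 2 groups of about 6 families each; 3 age bands; unadjusted *t* test.

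**Assumptions (not in the protocol).**
- The split of locations between types is 3 to 2, with 4 to 1 as the alternative.
- Banding is strict: each location runs two different bands, every pair equally likely. The protocol does not require this, so the result marks the unfavourable end.
- EAS band effects are 0, 0.25 and 0.5 SD from youngest to oldest. The protocol gives no figure for how any score depends on child age.

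**Step 1. Enumeration.** Each location has 3 possible pairs of bands, so five locations give 3^5 = 243 assignments. For each one:

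bias = Σ over bands of (share in type A − share in type B) × band effect

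| Quantity | 3 v 2 locations | 4 v 1 locations |
|---|---|---|
| Mean signed bias | 0 | 0 |
| Mean absolute bias | 0.075 SD | 0.097 SD |
| Median absolute bias | 0.063 SD | 0.094 SD |
| Maximum | 0.25 SD | 0.25 SD |
| Assignments with bias above 0.1 SD | 33% | 42% |
| Mean largest gap in a band's share | 26 points | 33 points |

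The maximum can be checked by hand. If one type runs only the two youngest bands, its mean effect is (0 + 0.25)/2 = 0.125. If the other runs only the two oldest, it is (0.25 + 0.5)/2 = 0.375. The difference is 0.25 SD.

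With band midpoints of 2.5, 9 and 15.5 years, the mean absolute age gap is about 2.0 years (3 v 2) or 2.5 years (4 v 1).

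**Step 2. Comparison with sampling error.** With 36 v 24 families, the standard error of a standardised difference, ignoring clustering, is √(1/36 + 1/24) = 0.26 SD. The typical bias is 0.075/0.26 ≈ 0.29 of a standard error, and the worst case is 0.25/0.26 ≈ 0.95.

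**Step 3. Effect on the test.** The unadjusted two-sided 5% test was simulated with no true location effect (4,000 runs per setting, 12 families per location, both splits).

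| Age effect per band | Strict bands | Mixed-age groups, ages alike across sites |
|---|---|---|
| 0 | 5.0–5.1% | 4.8–5.1% |
| 0.25 SD (0.5 SD youngest to oldest) | 5.7–6.0% | 4.7–5.2% |
| 0.5 SD (1.0 SD youngest to oldest) | 7.9–8.2% | 4.7–5.1% |

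**Step 4. If groups mix ages.** In the same simulation (3 v 2) the between-type gap in mean band has an SD of 0.214 bands, against 0.367 under strict banding. At 0.25 SD per band this gives 0.214 × 0.25 = 0.05 SD against 0.367 × 0.25 = 0.09 SD. With mixed ages the remaining imbalance is ordinary sampling variation, which the *t* test already allows for.

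**The case against.** A reader might infer from two groups and three bands that each location can serve only two bands, so that child age must differ between location types and must confound the comparison. The protocol does not support that. The bands are expressly a guideline, groups may mix ages, and no eligible age is shut out of any location. Nothing ties a band to a location type, and even under strict banding the average bias is zero. The objection stands to this extent: the right words are that child age may differ, in no expected direction.

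It can also be said that objective 4 is descriptive and that an unadjusted difference answers it. That stands too, and is why the unadjusted estimate should be kept. It does not make the adjusted one superfluous, because the Background and Objectives give living circumstances as the reason to expect a difference.

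The typical bias is also under a third of a standard error in a pilot that already warns about its small convenience sample. This is correct and limits the weight of the point. The general caution does not name child age, however, and describing demographics for all participants would not by itself show their balance by location type.

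Finally, requiring every band to run in each location type may be unworkable: a type with a single location has only two groups, and families relocate often. This stands, and no such requirement is proposed.

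**Conclusion.** The point holds in a limited form. The comparison is fixed as unadjusted, nothing described balances child age between location types, and child age is a plausible source of distortion, mainly for the EAS.

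Under strict banding, a 3 to 2 split and a 0.5 SD youngest-to-oldest gradient, the typical bias is about 0.06 to 0.08 SD, with a maximum of 0.25 SD; at 4 to 1 it is typically 0.09 to 0.10 SD. Type I error would be about 6%, rising to about 8% if the gradient were twice as steep. With mixed-age groups and similar ages across sites, there is no inflation from this mechanism. Local recruitment that produced different ages at different sites would fall outside that last case, and the protocol gives no basis for sizing it.

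The size of the problem therefore rests on assumptions about banding, the location split and the age gradient that the protocol neither states nor excludes. The case for acting is that the remedy costs almost nothing and makes the comparison easier to interpret.

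**What to change.** 1. Report child age (for the EAS, the age of the child in the filmed dyad) and parent education by location type.
2. Keep the unadjusted difference for objective 4. Beside it, give a regression estimate of the location-type difference adjusted for child age, with a confidence interval, chiefly for the EAS.
3. Show time in the Netherlands and country of origin by location type, but treat them separately and do not adjust for them by default. They may be part of what living in a family facility means.
4. State in the limitations that child age may differ between location types.

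**Cost.** One or two degrees of freedom and slightly more analysis work. Family members' ages and educational level are already collected. Recruitment and group scheduling do not change.
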